## Abstract

**Background:**

In recent years, the rapid increase in gastrointestinal endoscopic procedures has posed new demands and challenges for painless and comfortable medical care. Intravenous anesthetics may increase postoperative euphoria in patients. This study aims to evaluate the effects of intravenous propofol combined with fentanyl, nalbuphine, or saline on euphoria in patients undergoing painless gastrointestinal endoscopy.

**Methods:**

This is a single-center, randomized, double-blind, placebo-controlled trial protocol involving 285 adult patients scheduled for bidirectional endoscopy. Participants will be randomly assigned to either the fentanyl group, the nalbuphine group, or the placebo group (n = 95 per group). The fentanyl group will receive propofol + fentanyl; the nalbuphine group will receive propofol + nalbuphine; and the placebo group will receive propofol + saline. The primary outcome is the Addiction Research Center Inventory (ARCI) - Morphine–Benzedrine Group (MBG) scores at 30 min post-awakening. Secondary outcomes will include ARCI-MBG scores at 1 week and 1 month postoperatively; ARCI total scores at 30 min post-awakening, 1 week, and 1 month postoperatively; ARCI-Pentobarbital, Chlorpromazine, Alcohol Group (PCAG) scores at 30 min post-awakening, 1 week, and 1 month postoperatively; ARCI-Lysergic Acid Diethylamide (LSD) scores at 30 min post-awakening, 1 week, and 1 month postoperatively; Pittsburgh Sleep Quality Index scores at 1 week and 1 month postoperatively; and dream descriptions (none, pleasant, or nightmare) at 30 min post-awakening; The Surgical Pleth Index assessed at the time of endoscope insertion. Safety outcomes will include desaturation, hypotension, nausea or vomiting, dizziness, headache, choking cough, involuntary movement, bradycardia, and airway intervention. Data will be analyzed following a modified intention-to-treat approach.

**Discussion:**

This study aims to provide high-quality evidence for the potential addictive properties and safety of propofol combined with opioids in gastrointestinal endoscopy procedures.

**Ethics and Dissemination:**

This study was approved by the Ethics Committee of Xiangcheng People’s Hospital of Suzhou (2024-KY-05) on 19 August 2024, and is registered with the Chinese Clinical Trial Registry (ChiCTR2500096595). All participants will provide written informed consent, and the study will adhere to the principles of the Declaration of Helsinki. The findings will be published in a peer-reviewed journal. URL: https://www.chictr.org.cn/showproj.html?proj=252367.

## 1 Introduction

Gastrointestinal endoscopy is an essential method for diagnosing and treating gastrointestinal diseases, with a large number of endoscopic examinations performed globally each year. In China, a national survey projects that, driven by an aging population, the number of painless gastrointestinal endoscopies will reach approximately 51 million by 2030 (Zhou et al., 2021). Two-way endoscopy, where esophagogastroduodenoscopy and colonoscopy are conducted simultaneously in a single visit, is gaining increasing acceptance among patients (Song et al., 2023; Choi et al., 2020). To enhance patient comfort and reduce the influence of patient movement on the quality and safety of endoscopic procedures, the use of sedatives is becoming increasingly common (Dossa et al., 2021). Among the available sedatives, propofol, recognized for its rapid onset and recovery, has become one of the most widely used agents for painless gastrointestinal endoscopy worldwide (Lucendo et al., 2015; Goudra, 2019). Although severe respiratory and cardiovascular complications with propofol are relatively infrequent, both animal models and healthy volunteer studies have demonstrated its capacity to induce euphoria and suggested its possible involvement in dopaminergic signaling within the ventral tegmental area (VTA) and nucleus accumbens (NAc) (Nishizawa and Suzuki, 2018; Brechmann et al., 2018). Propofol has been shown to produce rewarding and reinforcing effects in animal studies, with evidence of self-administration and conditioned place preference, indicating its potential for abuse (Roussin et al., 2007). In humans, clinical trials reveal that propofol can induce euphoria and subjective feelings of pleasure, further supporting its potential for recreational use and addiction (Roussin et al., 2007). Consequently, these findings have raised concerns about propofol’s potential for drug dependence and addiction risk. In recent years, the increase in reported cases of propofol abuse has become a concerning trend, prompting some researchers to advocate for classifying propofol as a controlled substance (Uzbay and Shahzadi, 2024).

Propofol is widely used for sedation in various surgical patients, gastrointestinal endoscopic procedures, outpatient minor surgeries, and for sedation in ICU patients (McKeage and Perry, 2003; Hewson et al., 2021). Propofol, whether administered alone or in combination with opioid analgesics such as fentanyl or nalbuphine, is a common sedation strategy in digestive endoscopy (Sahinovic et al., 2018; Dossa et al., 2020). Fentanyl, a potent synthetic opioid, exerts its analgesic effects by activating μ-opioid receptors and enhancing dopamine release in the ventral tegmental area and nucleus accumbens—processes that induce both rewarding sensations and euphoria—and it also carries a risk of drug abuse (Kreek et al., 2019). Given fentanyl’s inherent ability to evoke euphoria, we hypothesize that its co-administration may further augment propofol’s euphoric effect. In contrast, nalbuphine, a mixed agonist–antagonist that primarily acts as a κ-opioid receptor agonist and partially antagonizes μ-opioid receptors, rarely causes euphoria and displays minimal drug-seeking behavior or physiological dependence, suggesting a low potential for abuse (Raghav et al., 2018). Accordingly, we propose that nalbuphine’s partial μ-opioid receptor antagonistic properties might help mitigate propofol’s excitatory or euphoric effects. Gastrointestinal endoscopy is widely performed and frequently repeated (Akarsu Ayazoglu and Uzman, 2021), yet there remains a lack of comprehensive clinical research examining whether co-administration of propofol with different opioids results in distinct euphoria-related responses. This study aims to investigate whether propofol co-administered with fentanyl or nalbuphine differentially influences euphoria in patients undergoing gastrointestinal endoscopy. By thoroughly evaluating the impact of these sedation strategies, we hope to provide valuable insights and potentially set a new standard for painless endoscopic procedures, thereby improving patient safety and overall outcomes.

## 2 Methods

This protocol adheres to the Standard Protocol Items: Recommendations for Interventional Trials (SPIRIT) guidelines.

### 2.1 Study design and patients

This study is a single-center, prospective, randomized, double-blind, placebo-controlled, parallel-group clinical trial. The trial will be conducted at the Suzhou Xiangcheng People’s Hospital, enrolling a total of 285 patients. Recruitment is scheduled to take place from 15 February 2025 to 31 August 2025. The study flow diagram is shown in Figure 1.

**FIGURE 1 F1:**
[figure not shown]
Study flow diagram. Intervention: Three groups were administered 0.5 μg/kg of intravenous propofol along with either 0.03 mg of fentanyl, 3 mg of nalbuphine, or an equivalent volume of saline to induce sedation. Throughout the procedures, sedation was adjusted by titrating propofol doses, typically ranging from 0.2 to 0.3 mg/kg, to maintain the predetermined sedation level.

### 2.2 Inclusion criteria

Patients who meet the following criteria will be included:• Aged from 18 to 75 years old;• Body mass index (BMI) 18–30 kg/m^2^;• ASA grade I-III;• Mallampati grade I-III;• Patients undergoing bidirectional endoscopy• Patients can understand the whole process of this clinical study and sign the informed consent.

### 2.3 Exclusion criteria

The exclusion criteria include:• Complicated with serious heart, lung or brain diseases;• Patients with severe sleep apnea syndrome;• Patients with severe esophageal and gastric motility diseases;• Long-term use of opioids or hypnotics and significant dependence on sedative or analgesic drugs. Long-term opioid use;• Patients allergic to propofol, fat emulsion, soy, or egg;• Pregnant or lactating women;• Language communication disorder, lack of cooperation, inability to communicate, or mental disease;• Mallampati grade IV, mouth opening < 2.5 cm; Patients who might have or had a history of difficult airway or had a history of abnormal anesthesia recovery were predicted;• Chronic alcoholics

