### 2.7 Randomization and blinding

An independent researcher will generate random numbers using an online tool (https://www.sealedenvelope.com/simple-randomiser/v1/lists) with a 1:1:1 allocation ratio. The randomization results will be stored in sealed, opaque envelopes. Patients will be assigned to the fentanyl, nalbuphine, or placebo group. A nurse anesthesiologist not involved in other study procedures will prepare fentanyl, nalbuphine, and saline in syringes labeled only with patient numbers, which will also be marked on the outer packaging. Patients, surgeons, anesthesia providers, outcome assessors, and statisticians will all be blinded to group assignments.

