### 2.9 Anaesthetic care

Venous access was established immediately after the patient entered the examination room, and vital signs were monitored. Intraoperative monitoring included non-invasive blood pressure (NIBP), electrocardiography (ECG), and pulse oximetry (SpO_2_). Oxygen was administered via a nasal cannula at a flow rate of 3 L/min until patients completed the gastroscopy and were fully awake. Anesthesia for the three groups of patients was induced with an intravenous injection of propofol at 1.5–2.5 mg/kg, combined with either fentanyl (0.05 mg), nalbuphine (5 mg), or an equivalent volume of saline. Sedation was adjusted throughout the procedures by titrating propofol doses, typically 0.2–0.3 mg/kg, to achieve the desired sedation level. At the start of esophagogastroduodenoscopy, the target sedation level was set at a Modified Observer’s Assessment of Alertness/Sedation (MOAA/S) scale score of 1 (responsive only to a trapezius squeeze stimulus). During the subsequent colonoscopy, the target sedation level was adjusted to a score of 2 (responsive only to prodding or shaking). Hypotension, defined as a systolic blood pressure of <80 mm Hg or a 30% decrease from baseline, and bradycardia, defined as a heart rate <45 beats/min, were treated as necessary. If SpO_2_ fell below 90% for 10 s or more, supplemental oxygen at 5–10 L/min was administered, and airway interventions, such as jaw thrust, oral or nasal airway placement, or endotracheal intubation, were performed as needed.

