This study has several limitations. First, as a single-center trial, the generalizability of the results to broader clinical settings may be limited; multi-center studies involving diverse patient populations would be necessary to validate these findings. Second, the relatively short follow-up duration (1 month) restricts the evaluation of potential long-term euphoric effects and addiction risks associated with repeated exposure to propofol and opioid combinations. Extended follow-up periods would provide deeper insights into the chronic implications of these sedation regimens. Third, the exclusion criteria—especially excluding patients with long-term opioid or sedative usage—may introduce selection bias, limiting the external validity of the results. Including such patient groups in future research could yield a more comprehensive understanding of drug-related addictive risks. Fourth, the primary outcomes of this study rely on subjective self-reported measures of euphoria, which might be susceptible to response bias; incorporating objective biomarkers or neuroimaging techniques in future studies could enhance the objectivity of the findings. Lastly, the current study design does not include objective behavioral assessments of addiction-related behaviors, such as drug-seeking actions, thereby limiting the evaluation of true addiction potential. Future investigations should explore other sedative drug combinations and their potential effects on euphoria, as well as further examine objective behavioral events related to addiction.

The primary aim of this randomized, double-blind, placebo-controlled trial is to evaluate the differential effects of intravenous propofol combined with fentanyl, nalbuphine, or placebo on patient-reported euphoria following painless gastrointestinal endoscopy. By systematically examining the impact of these sedation regimens, the study seeks to determine whether fentanyl amplifies, or nalbuphine mitigates, propofol-induced euphoric sensations. The findings are anticipated to provide robust clinical evidence to guide sedation strategies, potentially optimizing postoperative sedation protocols and enhancing patient safety and outcomes in gastrointestinal endoscopic practice. Additionally, if the results confirm that nalbuphine reduces euphoria compared to fentanyl, this could lead to safer sedation protocols by minimizing the risk of addiction-related side effects.

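### The allergy exclusion leaves out fentanyl and nalbuphine, the two drugs assigned at random

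*Protocol article*

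**What the plan says.** Section 2.3 of the protocol article contains one allergy criterion: "Patients allergic to propofol, fat emulsion, soy, or egg". The only exclusion that mentions opioids is "Long-term use of opioids or hypnotics and significant dependence on sedative or analgesic drugs", followed by a repeat of long-term opioid use. The limitations paragraph in section 3 describes that item in the same terms, as "excluding patients with long-term opioid or sedative usage".

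The Abstract (Methods) states the randomised comparison: "Participants will be randomly assigned to either the fentanyl group, the nalbuphine group, or the placebo group". Section 2.7 sets this up "with a 1:1:1 allocation ratio", with syringes identified only by patient number and with patients, anaesthesia providers and assessors blinded. Section 2.9 has propofol given to everyone, "combined with either fentanyl (0.05 mg), nalbuphine (5 mg), or an equivalent volume of saline". Section 2.8 gives different opioid doses, but the dose does not matter here.

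**The concern.** The allergy item is detailed enough to list individual ingredients and foods, yet it covers only one of the three active drugs in the trial. The two it omits are those that patients receive by chance and under blinding.

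Blinding is why the written criterion matters. In ordinary care, an anaesthetist who hears of a fentanyl allergy chooses another drug. Here the provider does not know what is in the syringe, so a known allergy can be acted on reliably only by keeping the patient out before allocation. The printed list gives no criterion for doing that. If a reaction occurs, section 2.14.2 routes emergency unblinding through a request from the principal investigator to the data monitoring committee, so prevention at screening is the better safeguard.

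What is at stake is the safety of a very small number of patients. The primary outcome, the sample size and the analysis are unaffected.

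**Working it through.** The first part of the check is textual, because the plan gives no figure on this point to reproduce.

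**Does any other criterion cover allergy to the opioids?**

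- Section 2.2 (inclusion): age, BMI, ASA grade, Mallampati grade, bidirectional endoscopy, and understanding with consent. Nothing on allergy or contraindication.
- Section 2.3, opioid item: long-term use and dependence. Someone who reacted to a single past dose of fentanyl does not meet it.
- Section 2.3, airway and anaesthesia-history item: difficult airway and abnormal recovery, not drug allergy.
- Section 2.3, remaining items: serious heart, lung or brain disease; severe sleep apnoea; oesophageal and gastric motility disease; pregnancy or lactation; communication problems or mental disease; chronic alcohol use.
- Sections 2.7 to 2.10 (randomisation, interventions, anaesthetic care, data collection): no allergy criterion.

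So, as printed, a known allergy to fentanyl or nalbuphine does not exclude a patient.

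**How many patients could this touch?**

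Inputs from the document: 95 per group, 285 in total, allocation 1:1:1. Inputs not in the document, and therefore assumed:

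- *p*, the prevalence of known allergy per drug among those enrolled, 0.05% to 0.5%, taken as the same for both drugs for simplicity;
- *c*, the share of such patients whom the routine history would catch, 50% to 90%.

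1. Chance that an enrolled patient allergic to one opioid is allocated it: 95/285 = 1/3. If allergic to both, chance of being allocated one of them: 190/285 = 2/3. Neither figure needs a prevalence.
2. Expected allocations to a known allergen if nobody acts on the history: 285 × *p* × 1/3 = 95*p* per drug, so 190*p* over both.
   - *p* = 0.0005: 95*p* = 0.0475 and 190*p* = 0.095.
   - *p* = 0.005: 95*p* = 0.475 and 190*p* = 0.95.
3. Allowing for the history, 190*p*(1 − *c*):
   - lowest: 0.095 × 0.1 = 0.0095;
   - highest: 0.95 × 0.5 = 0.475.
4. Patients removed by adding both drugs, if no one is allergic to both: 285 × 2*p* = 0.285 to 2.85.
5. Extra screening needed to keep 285 enrolled: 285/(1 − 2*p*) − 285 = 0.285 to 2.88.

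**The case against.** The strongest objection is that this rests on silence in a condensed article. The list opens with "The exclusion criteria include", which does not declare it closed, whereas section 2.2 is worded as a complete set ("Patients who meet the following criteria will be included"). The full protocol or eligibility form may name the opioids, in which case the trial has no gap and only the article does. That possibility stands and limits confidence. It does not dispose of the point. The article does not pass over allergy or summarise it as allergy to study drugs; it prints a specific list. Condensation is a weak explanation for a list that keeps egg and drops both drugs under test.

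A second objection is that the consequence is negligible. Once an assumed history catch rate is included, the expected count stays below one patient and spans a 50-fold range (0.0095 to 0.475) produced entirely by assumptions. Patients attend a pre-operative visit and are treated under monitoring, and nothing shows that a patient with a declared opioid allergy would actually be dosed. This is fair and sets the priority: the point is a small one. It does not make the printed rule right, because a history protects the patient only if it leads to exclusion, and the list gives no ground for that.

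Third, the trial already has ethics approval, registration and a fixed recruitment window (15 February to 31 August 2025), so changing eligibility may be more than an edit. This also stands, and the amendment is counted in the cost of the fix.

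**Conclusion.** The concern holds for the text as published. The single allergy criterion covers propofol, fat emulsion, soy and egg and neither randomised opioid, and no other printed criterion fills the gap. Followed literally, section 2.3 admits a patient with a known allergy to a drug they may then be given blind, with probability 1/3 (2/3 of receiving one or other drug if allergic to both).

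The expected number affected is small: at most 190*p* over both drugs, which is about 0.1 to 1.0 patients under the assumed prevalence, and about 0.01 to 0.5 if the history catches 50% to 90% of cases. Prevalence and catch rate are assumptions, not figures from the documents. Confidence is medium because the full protocol is not shown. The point is worth correcting for safety, and it has no bearing on the power, the significance level or any treatment comparison.

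**What to change.** Add fentanyl and nalbuphine to the allergy item in section 2.3, next to propofol, and to the screening form. Apply it at the pre-operative eligibility check, which Table 1 already places before allocation. First confirm what the full protocol says. If it already excludes these allergies, only the published list needs the two names.

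The cost is two added drug names, plus a routine amendment if the full protocol has the same omission. The patients lost are those allergic to either drug. They are excluded before allocation and can be replaced, so 285 stands, at about 0.3 to 2.9 extra patients screened under the assumed prevalence.

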### 2.4 Primary outcome

The primary outcome will be the Addiction Research Center Inventory (ARCI) - Morphine–Benzedrine Group (MBG) scores, assessed via in-person interviews at 30 min post-awakening. The ARCI scale was developed by the National Institute of Mental Health Addiction Research Center (United States). The MBG, a subscale of the ARCI, measures drug-induced euphoria and helps assess whether patients experience euphoria. The MBG consists of items 1 to 16, and the sum of these items represents the euphoria score. The Chinese version used in this study was translated by experts, with its reliability and validity confirmed.

### 2.5 Secondary outcomes

Secondary outcomes will include ARCI-MBG scores at 1 week and 1 month postoperatively; ARCI total scores at 30 min post-awakening, 1 week, and 1 month postoperatively; ARCI-Pentobarbital, Chlorpromazine, Alcohol Group (PCAG) scores at 30 min post-awakening, 1 week, and 1 month postoperatively; ARCI-Lysergic Acid Diethylamide (LSD) scores at 30 min post-awakening, 1 week, and 1 month postoperatively; Pittsburgh Sleep Quality Index scores at 1 week and 1 month postoperatively; and dream descriptions (none, pleasant, or nightmare) at 30 min post-awakening; The Surgical Pleth Index assessed at the time of endoscope insertion.

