### 2.8 Study interventions

In this study, patients will receive intravenous propofol combined with either fentanyl, nalbuphine, or saline during painless gastrointestinal endoscopy. Patients in the fentanyl group will receive a combination of propofol and fentanyl, those in the nalbuphine group will receive propofol and nalbuphine, and the placebo group will receive propofol with saline. All patient groups were administered 0.5 μg/kg of intravenous propofol along with either 0.03 mg of fentanyl, 3 mg of nalbuphine, or an equivalent volume of saline to induce sedation. Throughout the procedures, sedation was adjusted by titrating propofol doses, typically ranging from 0.2 to 0.3 mg/kg, to maintain the predetermined sedation level. At the start of esophagogastroduodenoscopy, the target sedation level was set at a Modified Observer’s Assessment of Alertness/Sedation (MOAA/S) scale score of 1 (responding only to trapezius squeeze stimulus). During the subsequent colonoscopy, the target sedation level was set at a score of 2 (responding only to prodding or shaking stimuli). All medications will be administered by medical professionals who are not involved in patient recruitment or data collection to maintain blinding. Randomization will be performed prior to the start of the study by an independent researcher using a computer-generated randomization table, and group assignments will be stored in sealed opaque envelopes to ensure blinding of patients, investigators, and data analysts. The study schedule for patient enrollment, interventions, and outcome assessments will follow the SPIRIT statement (Table 1). All endoscopy procedures will be performed by experienced endoscopists who have conducted at least 1,000 gastrointestinal endoscopies procedures to the study.

**TABLE 1 T1:** Schedule of patient enrolment, study interventions and outcome assessment.

Time point	Study period						
	Enrolment	Allocation	Post-allocation			Follow-up	Follow-up
	Pre-op visit	Pre-op	Intra-op	Post-op	30 min post-awake	1 week	1 month
Patient enrolment							
Eligibility criteria	×						
Written informed consent	×						
Demographic data	×						
Baseline characteristics	×						
HADS	×						
Randomization/allocation		×					
Study interventions							
Propofol + fentanyl		×					
Propofol + nalbuphine		×					
Propofol + saline		×					
Outcome assessment							
ARCI-MBG					×	×	×
ARCI-PCAG					×	×	×
ARCI-LSD					×	×	×
ARCI-Total					×	×	×
PSQI						×	×
Dream descriptions					×		

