### 2.10 Data collection and monitoring

Data collection will include baseline characteristics such as age, sex, BMI, comorbidities, smoking status, alcohol consumption, education level, and scores from the Hospital Anxiety and Depression Scale (HADS), as well as the number of painless examinations. All data will be documented in case report forms (CRFs) and subsequently entered into the electronic database under the supervision of the principal investigator. An independent Data Monitoring Committee (DMC) will continuously monitor the data collection process. Once data registration is complete, the electronic database will be secured. De-identified datasets will be provided to an independent statistician for analysis based on a predefined plan. Serious adverse events (SAEs), related or unrelated to the study medication (e.g., persistent severe psychiatric symptoms), must be promptly reported to the principal investigator. The perioperative care team will take necessary actions to ensure participant safety, and these events must be reported to the DMC within 24 h for further evaluation and possible adjustments or study termination. To ensure the integrity and accuracy of the collected data, we implemented the following measures: A double-check mechanism for data entry, where all data entries are verified by a second independent researcher; Regular audits of the collected data to identify and correct any inconsistencies or errors; Standardized training for all researchers involved in data collection to ensure consistent protocols and reduce the risk of errors.

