### 2.12 Statistical analysis

The normality of continuous variables will be evaluated using the Shapiro-Wilk test. Variables following a normal distribution will be reported as mean (standard deviation), while non-normally distributed variables will be expressed as median (interquartile range). The continuous data of normal distribution were analyzed by 1-way analysis of variance, and the continuous data of nonnormal distribution among the three groups were analyzed by the Kruskal-Wallis rank-sum test. Categorical data were analyzed using the χ^2^ test or Fisher’s exact test, and the P value was adjusted according to Bonferroni method and fixed at 0.017 for pairwise comparison. P < 0.05 was considered to indicate significance.

Outcome analyses for the primary endpoint will primarily follow a modified intention-to-treat (mITT) approach, including all participants for whom relevant data are available, regardless of protocol adherence. Additionally, a per-protocol (PP) analysis will be conducted, excluding participants with protocol deviations or those who withdrew consent, to evaluate the treatment effect among those who strictly followed the study protocol. The primary outcome is the ARCI-MBG score measured 30 min post-awakening. To account for potential confounders, a covariate-adjusted linear mixed model (LMM) will be utilized. The model will incorporate fixed effects for group (treatment group), time points (30 min post-awakening, 1 week, and 1 month), and the interaction between group and time to evaluate differences across groups over time. Potential confounders, including HADS scores, sex, age, BMI, comorbidities, smoking status, alcohol consumption, education level, and the number of painless examinations, will be included as covariates in the model. Sensitivity analyses will be conducted using both mITT and PP approaches to evaluate the robustness of the findings. Additionally, these analyses will adjust for potential confounders such as sex, age, BMI, comorbidities, smoking status, and education level, to further assess the consistency of the results across different analytical methods. No interim analysis will be planned. Missing data will not be imputed. Statistical analyses will be conducted with the use of SPSS software (V.25.0; IBM SPSS).

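### No pre-procedure ARCI-MBG or PSQI is collected, so scores cannot be adjusted for or read against the patient's own starting level; the between-arm comparison stays valid

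*Protocol article*

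**What the plan says.** **Outcome timing.** Section 2.4 has the primary ARCI-MBG score "assessed via in-person interviews at 30 min post-awakening". Section 2.5 adds later scores: "Secondary outcomes will include ARCI-MBG scores at 1 week and 1 month postoperatively", and "Pittsburgh Sleep Quality Index scores at 1 week and 1 month postoperatively". Table 1 agrees. The ARCI rows are marked at 30 minutes, 1 week and 1 month, the PSQI row at 1 week and 1 month, and none of them at the pre-operative visit.

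**Baseline data.** Section 2.10 states: "Data collection will include baseline characteristics such as age, sex, BMI, comorbidities, smoking status, alcohol consumption, education level", followed by "scores from the Hospital Anxiety and Depression Scale (HADS), as well as the number of painless examinations". HADS is the only questionnaire among these items and the only one in the pre-operative column of Table 1.

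**Model.** Section 2.12 plans a covariate-adjusted linear mixed model with group, time and their interaction. The "time points (30 min post-awakening, 1 week, and 1 month" all fall after the procedure. The covariates are listed as "including HADS scores, sex, age, BMI, comorbidities, smoking status, alcohol consumption, education level, and the number of painless examinations". That is nine, none of them a starting value of the outcome.

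**Reference arm.** In section 2.8, "the placebo group will receive propofol with saline". The other two arms receive propofol with an opioid, so every patient is exposed to propofol.

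**The concern.** The plan already commits to covariate adjustment, and a pre-operative visit with a questionnaire already exists. The one covariate of the same kind as the outcome, its own pre-drug value, is not collected. An analysis plan that is not shown could not repair this, since it cannot adjust for a score that the visit schedule omits.

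Two things are at stake.

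- **Precision.** A baseline score removes the part of the outcome variance that it predicts, and corrects for chance differences between arms in starting level.
- **Interpretation.** A 1-week or 1-month MBG or PSQI score cannot be called a change, a persistence or a return to the patient's usual level. Similar PSQI scores in all arms would fit no effect at all, or an equal shift in every arm. At 30 minutes, the share of an MBG score that is due to the drugs cannot be separated from the level the patient would have reported beforehand. Yet section 2.4 offers the subscale as a way to tell whether patients experience euphoria, and the Discussion frames the question around euphoria induced by propofol.

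**Working it through.** **Inputs.** From section 2.11: target difference d = 0.5 SD (0.5 × 2.22 = 1.11 MBG points), two-sided alpha 0.017, power 80%, dropout 10%, 95 per group. Alpha is printed once with a percent sign; the formula uses 0.017, and so do I. The baseline-outcome correlation r is not in the document and is an assumption here, shown over a range.

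**Step 1: the plan's own figure.** n = 2(z₁₋α/₂ + z₁₋β)²/d²

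- With z = 2.387 and 0.842: n = 83.4. With the printed 2.396: 2 × (2.396 + 0.842)²/0.25 = 83.9. Both round up to 84 per group.
- With dropout: 84/0.9 = 93.3, so 94 per group and 282 in total. The stated 95 and 285 are consistent with this.
- Evaluable after dropout: 95 × 0.9 = 85.5, taken as 85. Power = Φ(0.5/√(2/85) − 2.387) = Φ(3.260 − 2.387) = 80.9%.

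The trial therefore meets its planned power without a baseline score.

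**Step 2: what a baseline score would add for the 30-minute MBG.** Adjustment leaves a residual SD of SD × √(1 − r²), so power = Φ(0.5/(√(1 − r²) × √(2/85)) − 2.387).

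| Assumed r | Variance removed (r²) | Power, 85 per arm | Difference detectable with 80% power | Evaluable n per arm for 80% power |
|---|---|---|---|---|
| 0 | 0% | 80.9% | 0.495 SD | 84 |
| 0.2 | 4% | 82.6% | 0.485 SD | 81 |
| 0.3 | 9% | 84.9% | 0.472 SD | 76 |
| 0.5 | 25% | 91.6% | 0.429 SD | 63 |

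These rows compare baseline adjustment with no adjustment at all. The plan already adjusts for nine covariates, and some of what a baseline score predicts will be shared with them, HADS above all. The gain over the actual plan is therefore best read as at most the difference between a row and the first row. Section 2.4 describes the MBG as a measure of drug-induced euphoria, so a low r at 30 minutes is plausible. At r = 0.2 to 0.3 the gain is 1.7 to 4.0 percentage points.

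**Step 3: chance imbalance.** The standard error of a pairwise difference in baseline mean is √(2/85) = 0.153 SD, giving a 95% range of ±0.30 SD. Its effect on the outcome is r times that: 0.3 × 0.30 = 0.09 SD at r = 0.3, and 0.5 × 0.30 = 0.15 SD at r = 0.5, against a target of 0.5 SD. This is random error that the unadjusted standard error already includes. It is neither bias nor an extra loss on top of step 2.

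**Step 4: PSQI and the later scores.** The document gives no SD, target difference or correlation for these, so no power figure can be computed. The r² rule applies in the same way. The interpretive gap does not depend on r.

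**The case against.** The strongest reply is that the trial asks a between-regimen question and is built to answer it. The Introduction and Discussion state the aim as a difference between regimens, and no outcome is defined as a change from baseline. Comparing randomised arms on post-treatment scores is a sound design, and step 1 shows that it is powered as planned. All of this stands.

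Three stronger readings are tempting, and the document does not support them.

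- **That the later scores have no reference level at all.** The randomised saline arm is a concurrent reference at every visit, and whether fentanyl raises or nalbuphine lowers the score can be judged against it. That arm isolates only the added opioid, however. It does not show how much of a score is due to propofol. The 1-month score cannot stand in as a baseline either, because it is taken after exposure and is itself an outcome.
- **That the missing score is the strongest covariate and would outdo the nine planned ones.** No correlation is given for any of them. The exclusions in section 2.3 (long-term opioid or hypnotic use, chronic alcoholism, mental disease) may also narrow the spread of starting scores.
- **That the primary comparison is biased or underpowered.** Randomisation keeps it unbiased in expectation, and power is 80.9%.

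A practical objection also has weight: patients who have seen the euphoria items before sedation may anchor on their first answers. Exposure would be equal across arms, so it would not favour one, but it could shrink differences between them.

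**Conclusion.** The point holds as a shortfall in precision and interpretability, not as a flaw in the validity of the primary analysis. Sections 2.4, 2.5, 2.10 and 2.12 and Table 1 agree that no pre-procedure ARCI-MBG or PSQI is taken. Adjustment for starting level, within-patient change and a drug-free reference are therefore all out of reach.

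For the 30-minute MBG the benefit of a baseline score is uncertain and may be small: power of 82.6% to 84.9% at r = 0.2 to 0.3, and 91.6% at r = 0.5, against 80.9% without it. These figures assume 85 evaluable per arm, alpha 0.017, a linear baseline-outcome relation and no contribution from the nine planned covariates. The firmer loss concerns PSQI and the 1-week and 1-month scores, which can be compared between arms but not related to the patient's usual state. The improvement is cheap and worth making if timing allows.

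**What to change.** **Change.** Add PSQI and the 16-item MBG to the pre-operative visit in Table 1 and to the baseline data in section 2.10, beside HADS. In section 2.12, include baseline MBG as a covariate in the mixed model for MBG, and baseline PSQI as a covariate in the PSQI analysis.

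**Timing.** Section 2.1 schedules recruitment from 15 February to 31 August 2025.

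- Not yet begun: adopt the change for all patients.
- Begun: collect the scores from the remaining patients and use them only in a supportive analysis, leaving the primary model as planned. The primary precision gain in the table would then not be realised.
- Closed: restrict claims to differences between arms, avoid the language of change, persistence or return to usual level, and add the absence of baseline scores to the limitations in the Discussion.

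**Cost.** A few minutes of questionnaire time per patient (my estimate; the document gives none) at a visit already planned, an edit to Table 1 and sections 2.10 and 2.12, and an ethics notification. The drawback is one prior exposure to the items, equal across arms, with the anchoring risk described above.
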